## Abstract

**Background:**

In patients with major depressive disorder (MDD), antidepressant response and remission rates are low, highlighting the need for new treatment approaches. Recently, the abundant literature linking inflammatory processes and depressive symptoms have led to the hypothesis that selecting treatment for MDD based on the patient’s inflammatory status could be a promising strategy to improve outcomes in patients suffering from MDD. The aim of the randomised control trial we propose is to investigate the antidepressant efficacy of the combined treatment of MDD with antidepressant medication plus anti-inflammatory medication in individuals with raised inflammation levels. For the first time, this study will prospectively test the efficacy of an antidepressant plus anti-inflammatory augmentation based on baseline inflammatory maker levels in MDD using a randomised controlled trial design.

**Methods:**

This study proposes to measure blood C-reactive protein (CRP) levels before the initiation of treatment in 200 participants with MDD. Study participants are then assigned into one of two study strata: either into the ‘Depression with inflammation’ stratum (CRP levels > 3 mg/L); or into the ‘Depression without inflammation’ stratum (CRP levels ≤ 3 mg/L). Within each of the two study strata, participants randomly receive either antidepressant medication alone (vortioxetine) plus anti-inflammatory medication (celecoxib) or vortioxetine plus placebo for six weeks. At the end of the treatment period, participants have the opportunity to continue vortioxetine alone for a six-month post-trial period. Clinical outcomes are measured at baseline, fortnightly during the treatment period and at the three-month and six-month post-trial visits. The primary outcome is change in MADRS score, with a primary endpoint of a score reduction by 50% from baseline to six weeks (end of augmentation treatment with celecoxib). Secondary clinical outcomes are changes in the cognitive dimensions of depression (cognitive function, emotion processing and social cognition). Biological outcome measures (levels of CRP and other inflammatory markers) are measured at baseline, after six weeks of treatment and at the six-month post-trial visit.

**Discussion:**

The current study will generate novel evidence for biomarker-based personalised antidepressant treatment selection based on patient inflammatory status before treatment.

**Trial registration:**

Australian New Zealand Clinical Trials Registry (ANZCTR), ACTRN12617000527369p. Registered on 11 April 2017.

**Electronic supplementary material:**

The online version of this article (10.1186/s13063-018-2829-7) contains supplementary material, which is available to authorized users.

## Background

It is estimated that antidepressant medications may have therapeutic efficacy in as few as one-third of patients with major depressive disorder (MDD) [1, 2]. Furthermore, antidepressant treatment is currently selected on the basis of clinical symptoms only, including reported symptoms and observable mental state changes, making it difficult for the clinician to select the right treatment.

Several studies have highlighted a role of inflammatory processes in the development of depressive symptoms in a subgroup of patients with MDD. The central nervous system (CNS) has long been considered an immune-privileged organ, but abundant evidence documents bi-directional communication with the peripheral immune system [3]. Inflammatory cytokines released peripherally by immune cells can reach the brain through humoral, nervous and chemical pathways and hence act within the CNS [4, 5]. In the brain, inflammatory cytokines lead to the activation of glial cells (i.e. microglia and astrocytes) and coordinate a set of behavioural changes referred to as sickness behaviour in sick individuals [6–8]. Cytokines are strong modulators of several biological systems involved in behavioural regulation, such as mood regulation [6, 9].

In the context of chronic inflammation, sustained brain immune cell activation and cytokine production can lead to the development of neuropsychiatric symptoms. Indeed, pro-inflammatory mediators can induce depressive symptoms, with up to 80% of interferon-α (IFN-α) treated patients suffering from mild to moderate depressive symptoms [10–14]. Interestingly, these symptoms can be prevented or treated with antidepressants [11, 15, 16]. Numerous studies have consistently associated inflammation and somatic diseases comprising inflammatory processes, such as infections and autoimmune diseases, with an increased risk of depression [17–22]. In addition, studies have consistently shown increased levels of pro-inflammatory markers among individuals with depression, particularly during acute phases [23–25]. Meta-analyses have gathered large evidence, particularly with C-reactive protein (CRP) [25, 26], interleukin-6 (IL-6) [23–27], tumour necrosis factor-α (TNF- α) [23, 24, 27] and IL-1 receptor antagonist (IL-1ra) [24–26] being elevated among patients with depression. Interestingly, levels of IL-6 decreased after treatment of the acute depressive episode [24]. Also of note is a recent brain imaging study, which found increased microglial activation, indicating neuroinflammation, among 20 individuals suffering an active depressive episode compared to 20 healthy matched controls [28].

Since depression is a very heterogeneous disorder, it is noteworthy that recent studies have suggested that inflammatory components may be used to characterise a specific subgroup of patients with depression. Baseline increased levels of pro-inflammatory markers such as CRP have been linked to greater depressive symptom severity in general [25, 29–33] and also to greater severity of symptoms, such as mood symptoms, interest, activity, suicidality and cognitive symptoms of MDD [30]. In addition, in a retrospective analysis of a clinical trial using the TNF-α blocker infliximab to treat depressive symptoms, it was suggested that moderately increased levels of CRP at baseline might be indicative of response to infliximab; however, the study was preliminary with a small sample size of 60 patients and the conclusion was based on 13 patients showing response and 11 patients showing no response to infliximab [34]. However, the proof of concept that CRP levels at baseline might be indicative of treatment response to anti-inflammatory treatments in depression has not been studied prospectively yet. This approach may help to identify those individuals who may benefit from a targeted treatment approach, potentially leading to more tailored and more effective treatment in groups of MDD patients. Moreover, a recent systematic review and meta-analysis of clinical trials recommended that the field now needs randomised controlled trials (RCTs), using depression as the primary outcome, in individuals with high inflammation levels [35]. This review also noted that targeting inflammatory markers would be a move towards novel, effective and personalised treatment of depression. Recent work from our group has addressed the issue of selecting treatment for MDD based on inflammation status. Two of these publications found emerging evidence that anti-inflammatory evidence may need to be tailored based on the patient’s inflammatory profile [36, 37]. In other recent work from our group, a systematic review of the efficacy of non-steroidal anti-inflammatory drugs (NSAIDs) in depression concluded that translation of using effective anti-inflammatory treatment has failed so far and that further work, such as the clinical trial we propose, is urgently needed to translate this potentially significant treatment to clinical practice and improve patients’ mental health outcomes in depression [38].

We therefore propose that testing CRP levels in a blood test before the commencement of treatment in patients with MDD will give clinicians an informative biomarker at hand to guide the selection of effective antidepressant treatment. CRP was chosen as the informative inflammatory marker not only because it can predict improvement in depressive symptoms following anti-inflammatory treatment [34] but also because CRP detection in the blood can be routinely done in pathology services and hence shows potentially high clinical utility. Vortioxetine was chosen as the antidepressant medication; since it has a recently obtained Therapeutic Goods Administration (TGA) indication in Australia for the treatment of MDD, it is more likely to be useful in severe depression [39] and is likely to be useful in enhancing the remittance of cognitive symptoms of depression [40]. It will be novel to investigate its potential immune-modulatory effects in secondary analyses. Celecoxib was chosen as the trial anti-inflammatory medication because of its ability to increase the efficacy of antidepressant medication when used as an augmentation strategy [41, 42]. This is a first adequately powered, RCT that prospectively tests the efficacy of an antidepressant plus adjunctive anti-inflammatory treatment based on baseline CRP levels in MDD. This approach will inform real-world treatment of depression based on a widely available blood test.

## Methods and design

### Objectives

The primary objective of this study is to investigate the antidepressant efficacy, measured by Montgomery–Åsberg Depression Rating Scale (MADRS) score, of the six-week combined treatment of MDD with antidepressant medication (vortioxetine) plus anti-inflammatory medication (celecoxib). We hypothesise that a higher efficacy and larger reduction in symptoms of depression will be observed after six weeks when treatment is combined (antidepressant and anti-inflammatory) compared to the treatment with antidepressant alone, in individuals with baseline inflammation (i.e. with baseline CRP levels > 3 mg/L). In addition, we hypothesise that no difference between treatments will be observed in individuals with no baseline inflammation (i.e. with baseline CRP levels < 3 mg/L) (see Table 1).

**Table 1 Tab1:** Objectives and hypotheses of the study. Table stating study objectives and hypothesis in a generic way and in a drug-specific way

	Generic way	Drug-specific way
Primary objective	To investigate the antidepressant efficacy of the 6-week combined treatment of MDD with antidepressant plus anti-inflammatory	To investigate the antidepressant efficacy of the 6-week combined treatment of MDD with vortioxetine plus celecoxib 400 mg
Primary hypothesis	A higher efficacy and larger reduction in symptoms of depression will be observed after 6 weeks when treatment is combined (antidepressant and anti-inflammatory) in individuals with baseline inflammation	A higher efficacy and larger reduction in symptoms of depression will be observed after 6 weeks when treatment is combined (vortioxetine and celecoxib 400 mg) in individuals with baseline inflammation
Secondary objective 1	To investigate the anti-inflammatory effects of a combined treatment of MDD with antidepressant and anti-inflammatory in individuals with baseline inflammation (CRP levels > 3 mg/L) over a 6-week period	To investigate the anti-inflammatory effects of a combined treatment of MDD with vortioxetine and celecoxib 400 mg in individuals with baseline inflammation (CRP levels > 3 mg/L) over a 6-week period
Secondary hypothesis	A larger reduction of circulating levels of the inflammatory marker CRP will be observed in the group of depressed patients who are treated with antidepressant plus anti-inflammatory medication	A larger reduction of circulating levels of the inflammatory marker CRP will be observed in the group of depressed patients who are treated with vortioxetine plus celecoxib 400 mg
Secondary objective 2	To test whether there is evidence of a different effect of the combined treatment in the two inflammation strata	To test whether there is evidence of a different effect of the combined treatment with vortioxetine and celecoxib 400 mg in the two inflammation strata
Secondary objective 3	To investigate the safety of the anti-inflammatory treatment when combined with antidepressant	To investigate the safety celecoxib 400 mg treatment when combined with vortioxetine
Secondary objective 4	To investigate the effects of the antidepressant on cognition, psychosocial and workplace performance measures in MDD	To investigate the effects of vortioxetine on cognition, psychosocial and workplace performance measures in MDD

The secondary objectives of the study are:To investigate the anti-inflammatory effects of a combined treatment of MDD with vortioxetine and celecoxib in individuals with baseline inflammation (CRP levels > 3 mg/L) over a six-week period. We aim to demonstrate a larger reduction of circulating levels of the inflammatory marker CRP in the group of depressed patients who are treated with antidepressant plus anti-inflammatory medication (see Table 1).To test whether there is evidence of a different effect of the combined treatment in the two inflammation strata, although the study is not powered to detect this effect (see Table 1).To investigate the safety of the anti-inflammatory treatment of celecoxib 400 mg when combined with vortioxetine (see Table 1).To investigate the effects of vortioxetine on cognition (using the THINC-It tool) and on psychosocial and workplace performance measures in MDD (see Table 1).

### Recruitment and study design

A total of 200 patients with MDD will be included in the study. Recruitment and treatment take place in the wider Central Adelaide Local Health Network (CALHN), with all participant appointments being held in the Clinical Research Facility in the Health and Medical Sciences Building, Discipline of Psychiatry, University of Adelaide. In addition to this, and to ensure that required numbers of study participants are recruited, people from the general population who meet the inclusion criteria are able to engage with the proposed study, as it is made available through advertisement. Participants are free to withdraw from the study at any time.

The study is designed as a parallel group RCT with a superiority framework, investigating 200 participants with MDD over six weeks in the primary phase followed by a six-month post-RCT follow-up period (Fig. 1). The study proposes to measure the inflammatory marker CRP before the commencement of treatment. Following CRP measurement, study participants are then assigned into one of two study strata based on CRP levels. The first of these study strata is made up of 100 individuals with CRP levels > 3 mg/L (the ‘Depression with inflammation’ stratum) and the second study stratum is an active control, made up of 100 individuals with CRP levels ≤ 3 mg/L (the ‘Depression without inflammation’ stratum). In each stratum, participants are randomly allocated in a 1:1 ratio to augmentation of vortioxetine antidepressant treatment with either celecoxib or placebo. Following six weeks of concomitant administration of celecoxib or placebo with vortioxetine, the celecoxib or placebo is then stopped and the participants are treated with vortioxetine only for an additional two weeks. This allows the opportunity to assess the efficacy of taking vortioxetine alone. While the primary time point is the six weeks in which we compare vortioxetine with augmentation against vortioxetine without augmentation, following the RCT phase, all participants have the opportunity to continue on vortioxetine without celecoxib or placebo for another six months during a post-RCT observational study period.

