**Fig. 1 Fig1:**
[figure not shown]
Clinical timeline of the trial. Participants will complete assessment sessions fortnightly over the 8-week RCT period. “R” circles represent 1:1 random assignment of participants within each study stratum

The principal investigator (PI) and trial psychiatrist are aware which study participants are receiving celecoxib and which participants are receiving placebo, so that the dose of vortioxetine can be determined. An approximately twofold increase in vortioxetine plasma concentration has been observed following co-administration of bupropion, a strong CYP2D6 inhibitor [43]. When bupropion was added to vortioxetine 10 mg daily at steady state, a higher incidence of adverse events was observed than when vortioxetine was added to bupropion at steady state. This may be explained by pharmacodynamics or combined pharmacodynamic/pharmacokinetic effects following CYP2D6 inhibition with bupropion, which seem to be more pronounced when the inhibition is initiated when vortioxetine is in steady state than before vortioxetine is administered [43]. In the study where bupropion was added to vortioxetine, increased incidences of nausea, headache and vomiting were noted [43]. As celecoxib is also a strong inhibitor of CYP2D6, individuals receiving celecoxib start at a lower dose of vortioxetine, 5 mg daily, and are restricted to a maximum dose of 10 mg daily for the duration of co-administration. This is consistent with guidelines recommending the dose of vortioxetine be reduced by half if a strong CYP2D6 inhibitor is co-administered (Trintellix Product Monograph. Page 1 of 44, Lundbeck).

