Furthermore, dosage of vortioxetine will vary to a small extent between participants even in the same strata, treatment group and time point. This is due to differences in CYP2D6 metabolic functionality in the general population related to common genetic variants [44]. Unfortunately, testing for genetic markers of CYP2D6 dysfunction at baseline, or plasma concentration of vortioxetine in all participants at all necessary time points, is beyond the scope of this study. Nevertheless, we account for this in two ways. First, for the safety and comfort of participants, each person will be started on a low dose and only increase if and when acceptable tolerability is demonstrated, as measured by a low number and mild severity of side effects reported to trial researchers on an in-house side effects questionnaire. The possible doses by strata and treatment group are given in Fig. 2. We are also able to assume, using this method, that the plasma concentration is comparable between all participants throughout the trial [44]. Additionally, the variable of dose differences will be factored into statistical analysis by noting the cumulative total dose of vortioxetine per participant over the entire study.

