**Fig. 2 Fig2:**
[figure not shown]
Diagram stating the possible dosages of vortioxetine (antidepressant medication) and celecoxib (anti-inflammatory medication) within each group for all the periods of the trial

To promote participant retention, study participants are encouraged to contact the study team if any side effects cause them serious concern between appointments, allowing for the dosage of vortioxetine to be lowered if possible, in the hope of reducing the likelihood of early withdrawal from the study. In the case of early withdrawal from the study, all endpoint scales and blood collection will be conducted immediately for later analysis.

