According to stratified recruitment into the two treatment strata and the random allocation into two treatment groups, participants in both the ‘Depression with inflammation’ and ‘Depression without inflammation’ stratum receive celecoxib 400 mg daily or placebo. The starting dose of vortioxetine in both study strata is vortioxetine 5 mg daily for those receiving celecoxib, due to possible drug–drug interactions, and vortioxetine 10 mg daily for those receiving placebo. Two weeks after commencement of treatment, participants receiving vortioxetine 5 mg daily and 10 mg daily are provided the opportunity to increase to vortioxetine 10 mg or 20 mg daily, respectively, following an assessment by a research clinician (Fig. 2). The decision to increase the dose or to leave it the same is made by the trial psychiatrist after review of the change in depressive symptoms from baseline according to the MADRS and the presence and severity of side effects, rated by a blinded researcher. The dose of vortioxetine is increased only if the side effects experienced are easily manageable and the participants have not achieved recovery (MADRS score < 7). In study participants reporting symptoms consistent with an excessive plasma concentration of vortioxetine, the trial psychiatrist will reduce the dose of vortioxetine without informing the participant or blinded researchers administering scales. After six weeks of treatment, celecoxib and placebo are ceased, but the antidepressant vortioxetine is continued for at least two weeks. After the completion of the RCT phase, study participants are given the opportunity to continue taking vortioxetine into the post-RCT study phase for up to six months. Following an assessment by a research clinician, study participants who had been taking vortioxetine 5 mg or 10 mg daily during the RCT due to celecoxib co-administration are given the opportunity to increase to vortioxetine 10 mg and 20 mg daily, respectively; otherwise vortioxetine is continued in the post-RCT phase at the same dose as for the RCT phase.

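### On the visible text, the celecoxib arm keeps its halved vortioxetine dose for two weeks after celecoxib stops, so in that arm weeks 6–8 do not show vortioxetine alone at comparable exposure (minor)

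*Protocol article*

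**What the plan says.** The Recruitment and study design section describes what follows the six-week combination phase: "the celecoxib or placebo is then stopped and the participants are treated with vortioxetine only for an additional two weeks". It adds the reason: "This allows the opportunity to assess the efficacy of taking vortioxetine alone". The Fig. 1 caption fixes the length of the randomised phase: "Participants will complete assessment sessions fortnightly over the 8-week RCT period".

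The same section explains the dosing. Celecoxib is treated as a strong CYP2D6 inhibitor, so those who receive it start at 5 mg vortioxetine and are "restricted to a maximum dose of 10 mg daily for the duration of co-administration". The size of the interaction is taken from bupropion, for which an approximately twofold rise in vortioxetine concentration is cited. In the Study schedule section the placebo arm starts at 10 mg, and at week 2 "participants receiving vortioxetine 5 mg daily and 10 mg daily are provided the opportunity to increase to vortioxetine 10 mg or 20 mg daily", in that order.

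For week 6 the Study schedule section says that celecoxib and placebo cease and vortioxetine goes on for at least two weeks. It mentions no dose change at that point. The step from 5 to 10 mg or from 10 to 20 mg, for those who had been on the lower dose because of celecoxib, comes after the RCT phase is complete.

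On exposure, Recruitment and study design states: "We are also able to assume, using this method, that the plasma concentration is comparable between all participants throughout the trial". It also says that dose differences will be taken into the analysis through each participant's cumulative vortioxetine dose over the study. The Fig. 2 caption promises the possible doses "within each group for all the periods of the trial", but the figure itself is not available here.

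**The concern.** The halved dose is meant to offset the inhibitor. When the inhibitor is withdrawn and the dose stays halved, the offset becomes a deficit. In the former celecoxib arm two things then change together after week 6: celecoxib is gone, and the same tablet gives less vortioxetine exposure. If MADRS scores worsen between weeks 6 and 8, the reader cannot tell whether the loss of the anti-inflammatory drug or the weaker antidepressant exposure is responsible.

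What is at stake is the interpretation of this two-week phase in one arm per stratum. That is up to 2 × 50 = 100 of the 200 planned participants, fewer after withdrawals. The article gives the phase a purpose, and that purpose is only partly met.

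**Working it through.** **Inputs from the article.** Celecoxib arm: 5 or 10 mg vortioxetine. Placebo arm: 10 or 20 mg. Celecoxib stops at week 6. The RCT period lasts 8 weeks. Interaction multiplier: about 2, observed with bupropion and applied to celecoxib.

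**Assumption.** The multiplier for celecoxib itself, *m*, is not given, so it is varied from 2 down to 1 (no interaction). Exposure is taken as dose × *m* while celecoxib is on board, and as dose alone once inhibition has gone.

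**Step 1: reproduce the plan's own logic.** With *m* = 2, 5 × 2 = 10 and 10 × 2 = 20. These equal the placebo-arm doses, so the same-step exposure ratio up to week 6 is 1.0. The halving does what it is meant to do.

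**Step 2: when the reduced dose ends.** Study schedule puts the two-week continuation first, then completion of the RCT phase, then the offer of an increase. The Fig. 1 caption makes the RCT period 8 weeks. The Vortioxetine section's eight months of free medication over the RCT and post-RCT periods fits 8 weeks plus six months. On the visible text, the reduced dose therefore runs to week 8.

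**Step 3: weeks 6–8 with the dose held.**
- Same-step dose ratio, former celecoxib arm to placebo arm: 5/10 = 10/20 = 0.5, whatever *m* is.
- Across all combinations of scheduled doses: 5/20 = 0.25 to 10/10 = 1.0.
- Steady-state fall in exposure within the former celecoxib arm: 1 − 1/*m*.

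| *m* | Same-step exposure ratio to week 6 (*m*/2) | Same-step ratio after inhibition ends | Fall within the arm (1 − 1/*m*) |
|---|---|---|---|
| 2 | 1.0 | 0.5 | 50% |
| 1.5 | 0.75 | 0.5 | 33% |
| 1.25 | 0.625 | 0.5 | 20% |
| 1 | 0.5 | 0.5 | 0% |

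These are steady-state figures. The article does not say how fast inhibition fades, so the average fall over the two weeks is unknown.

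**Step 4: does recording cumulative dose repair this?** Take a participant held at 10 mg. Any 14 days add 14 × 10 = 140 mg to the total. With *m* = 2, 14 days on celecoxib correspond to 140 × 2 = 280 mg-equivalents, and 14 days after inhibition has gone correspond to 140. The recorded dose is the same while the exposure differs by a factor of two, so the covariate does not see the change.

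**The case against.** The strongest objection is that Fig. 2 exists to state the dose in every period and cannot be seen. If it sets the increase at week 6, the exposure problem as described does not arise, and only the Study schedule wording is out of line. That stands, and the point is conditional on it.

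A reader might also infer that the protocol contradicts itself about when the reduced dose ends. It does not. The restriction to 10 mg is a ceiling during co-administration and does not promise that the dose rises when co-administration ends. A ceiling that lapses at week 6 and an offer made after week 8 are compatible. Holding the dose for two weeks and then reassessing is a defensible clinical choice.

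A further tempting inference is that the trial's main result is compromised. The documents do not support this: "While the primary time point is the six weeks in which we compare vortioxetine with augmentation against vortioxetine without augmentation" places the primary comparison before celecoxib is withdrawn. No stated objective names week 8, and Results analysis describes no week-8 contrast between arms. The vortioxetine-alone aim is worded only as an opportunity.

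It can also be said that the comparability sentence belongs to a paragraph on genetic variation in CYP2D6, handled by titration, and that dose is carried into the analysis. Both are fair as context. But the sentence covers all participants and the whole trial, and dose in milligrams does not register the loss of inhibition.

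Finally, the twofold figure comes from bupropion. A weaker celecoxib interaction would give a smaller fall, down to none, which is why the range is shown.

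**Conclusion.** The point holds as a minor one, limited to weeks 6–8 in the former celecoxib arm. If Fig. 2 does not set an earlier increase, that arm stays on half the placebo arm's same-step dose after the only stated reason for halving has gone. On the protocol's twofold premise its steady-state vortioxetine exposure falls by 50%; with weaker assumed interactions the fall is 33% or 20%, and with no interaction it is nil. Except in that last case, a MADRS change there in weeks 6–8 cannot be attributed to celecoxib withdrawal alone. On the protocol's premise, plasma concentration is also not comparable throughout the trial, because parity is lost once inhibition ends. No effect on MADRS can be estimated from the article, and the speed of the fall is undocumented. The week-6 primary endpoint and the placebo arm's vortioxetine-alone reading are untouched.

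**What to change.** Three changes of wording are enough:

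1. Limit the statement on comparable plasma concentration to weeks 0–6.
2. Base the vortioxetine-alone assessment in weeks 6–8 on the placebo arm.
3. Treat any week-8 contrast between arms as descriptive.

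The cost is a narrower claim from this phase. No visits or participants are added.

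Offering the increase at the existing week-6 visit is an option for the investigators, not a requirement. The unblinded trial psychiatrist already sets the dose, and packages do not show it, so blinding would be kept. But it adds an optional, tolerability-selected dose change at the moment of withdrawal, and exposure could overshoot if inhibition fades slowly. If a share *u* accepts, the mean same-step dose ratio is 0.5(1 − *u*) + 1.0*u* = 0.5 + 0.5*u*: 0.75 at *u* = 0.5, and 1.0 only with full uptake. If this route is chosen, state whether the rule against increases after recovery (MADRS below 7) applies to it.

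If Fig. 2 already sets the increase at week 6, correct the Study schedule text to match.
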